## Methods/design

### Research aims

The specific aims of the LeSA Project are to: (1) test the effectiveness of the TBRI intervention and its different support formats – no in-home TBRI support, Structured Coaching, Responsive Coaching – on (a) preventing initiation and/or escalation of opioid use, (b) public health and public safety outcomes, (c) putative change mechanisms, including self-regulation, psychosocial functioning, and relationship with a safe adult; (2) document factors related to TBRI implementation and sustainment; and (3) estimate the start-up and implementation costs and cost-effectiveness of TBRI support options relative to standard re-entry practices in achieving lower rates of opioid initiation and reductions in healthcare and JJ system costs.

Primary hypotheses are as follows:
H1: Compared to youth receiving Standard Re-entry Practices (SRP) only, youth receiving TBRI in addition to SRP are less likely to initiate opioid use following discharge.H2: Compared to no in-home TBRI support, youth receiving Structured or Responsive Coaching are less likely to initiate opioid use following discharge, with the longest time to initiation occurring among youth receiving Responsive Coaching.H3: TBRI is most effective for preventing opioid initiation when facilities routinely use TBRI strategies within their residential settings, given increases in continuity as the youth transitions home from residential care.H4: The cost of implementing TBRI + SRP is higher than SRP alone, with higher cost-effectiveness when TBRI is added.

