#### Power

For H1 examining the effectiveness of SRP + TBRI compared to SRP alone, the proposed Intent to Treat (ITT) sample will include 360 youth/safe adult dyads (120 SRP, 240 TBRI), with 80 randomized to each TBRI condition. SAS PROC POWER for rank tests comparing 2 survival curves found that, if overall opioid initiation rates are 35% (SRP) vs. 25% (all TBRI groups) at any assessed time point, power is estimated to be at 93% (*α* = .05). For H2 comparing the 3 TBRI conditions, SAS PROC POWER for rank tests comparing 2 survival curves found that for sample sizes of 80 in each group, power = .80 when the hazard ratio = 1.57. When the combined TBRI groups are tested against SRP, power = .80 when the hazard ratio = 1.37.

For H3 and H4 pertinent to the organizational TBRI intervention, the expected sample (nine sites, up to 90 staff participants per site) and the response rate of 25% gives an expected sample of 203 participants. A small effect size (0.20), a power of 0.80, significance level of 0.05, and an intraclass correlation of 0.10 are used to calculate the minimum required sample size. Repeated measures design comparing staff participants over time results in a minimum sample size of 43 participants. To be more conservative, the same parameters are used for a mixed-effect design (four repeated measures by nine sites), yielding a minimum sample size of 189 participants.

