### Data analysis plan

For all analyses, an ITT approach is used, where all study participants are included in analyses. For H1 and H2, comparisons of survival curves for each group are performed using SAS PROC PHREG and PROC GLIMMIX using the log rank test with the Sidak multiple-comparison adjustment, with the primary outcome as the dependent variable. Differences between groups on secondary outcomes and change over time in implementation measures (e.g., TBRI use) are examined using repeated measures ANOVAs (SAS 9.4, PROC MIXED), with study site as random effects and condition, time, and interactions as fixed factors. Because SU rates are generally lower among JJ females, sex as a biological variable is examined as a moderator of differences in outcomes using univariate analyses (e.g., chi square, t-tests, ANOVA); when significant, tests of moderation are undertaken as part of all analyses. Putative change mechanisms are investigated as mediators of the Group – Primary Outcome relationship and structural equation modeling (SEM; using Mplus) is used to examine sex differences in mediation. For H3, changes in the outcomes over time are examined using repeated measures ANOVAs (SAS 9.4, PROC MIXED), with study site as random effects and time and time × site interactions as fixed factors. For H1–3, a log rank test is used to assess study dropout; stochastic multiple-imputation provides maximum likelihood estimates, accounts for uncertainty in missing values, and provides unbiased estimates of the treatment effect if data are missing at random.

Qualitative data from focus groups are transcribed and qualitatively coded (in Atlas.ti) by at least 2 research staff. An iterative process of coding and thematic analysis [84] are used to understand routine practices employed, nuances in the use of trauma-informed and child-centered strategies, facility facilitators/barriers to uptake of new interventions, general penetration of TBRI within the facility, and facility interest in sustaining and/or expanding TBRI practices.

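### The H3 model names study site as random but fixes time × site, so the random site term does nothing and the time test covers only these nine facilities

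*Protocol article*

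**What the plan says.** The Data analysis plan gives H3 its own model, a repeated measures ANOVA of change in outcomes, to be fitted in PROC MIXED. Its terms are described as follows: "with study site as random effects and time and time × site interactions as fixed factors". No fixed site main effect is listed, and the coding of time is not stated beyond the reference to ANOVA and factors.

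The same section gives secondary outcomes and change in implementation measures a different model, "with study site as random effects and condition, time, and interactions as fixed factors", in which no interaction with site is named.

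The Power section links H3 to the staff sample: "nine sites, up to 90 staff participants per site) and the response rate of 25% gives an expected sample of 203 participants". It sizes that sample with "A small effect size (0.20), a power of 0.80, significance level of 0.05, and an intraclass correlation of 0.10" and reports a "mixed-effect design (four repeated measures by nine sites), yielding a minimum sample size of 189 participants". So the H3 outcomes are most naturally read as staff measures taken at four surveys, although the H3 analysis sentence says only that outcomes are examined. H3 itself, under Research aims, reads "TBRI is most effective for preventing opioid initiation when facilities routinely use TBRI strategies within their residential settings".

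**The concern.** Declaring site random treats the nine facilities as a sample from a wider set. Fixing time × site treats them as the whole set of interest. The two choices imply different error terms for the time effect, and the sentence makes both.

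This matters because the sites can be expected to change at different rates:

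- **Starting point.** Three had used TBRI for one to three years at project start, two knew it without using it, and four did not know it (Study samples and recruitment).
- **Uptake.** Facility-wide TBRI is optional, with extra coaching and practitioner training only for sites that choose it, at any time (Support for the organizational TBRI intervention).
- **Timing.** Sites start in three waves, and the control stage lasts 8 to 12 months (Overall study design; Hybrid design: effectiveness trial).

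If change differs between sites and a result is then reported as a finding about juvenile justice facilities in general, the p-value for time would be too small.

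**Working it through.** **Inputs from the article.** 9 sites, 4 staff surveys, 203 expected staff (9 × 90 × 0.25 = 202.5), nominal level 0.05.

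**Assumed, not in the article.** Person variance 0.4 and residual variance 0.5, with total variance about 1; site-by-time variance v from 0 to 0.10; all 203 staff answer all four surveys.

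**The plan's own figure.** The minimum of 189 is not in dispute. One route, which the article does not state, gives it exactly. A within-subject F test with effect size 0.20, four measures and correlation 0.10 needs 63 people. The design effect for 21 staff per site is 1 + (21 − 1) × 0.10 = 3.0, and 63 × 3.0 = 189.

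**Step 1: can the site variance be estimated?** With time categorical, time plus time × site spans all 9 × 4 = 36 cells.

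- The rank of the fixed design is 36, and it is still 36 after the nine site columns are added.
- The REML criterion is the same (512.0634) at site variances 0, 0.05, 0.1, 0.5 and 2. The data say nothing about this variance.
- If time were a linear covariate, the rank would rise from 10 to 18 and the variance could be estimated. The result therefore depends on categorical time.

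**Step 2: which error term does time get?**

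- As written, staff-level residual: (203 − 9) × (4 − 1) = 582 df.
- With site × time random: (9 − 1) × (4 − 1) = 24 df.

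**Step 3: does a shared site level do harm?** No. With v = 0, simulated type I error was 5.1%, 4.8% and 5.2% at site variance 0, 0.1 and 1. The fixed cells absorb it.

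**Step 4: what if sites change differently and the claim goes beyond them?** With n = 203/9 = 22.6 staff per site, the time mean square is inflated by k = 1 + n·v/0.5, while the denominator still estimates 0.5. The true rejection rate is then P(F(3, 582) > 2.62/k), where 2.62 is the nominal 5% cut-off.

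| v | k | formula | simulated, as written | simulated, site × time random |
|---|---|---|---|---|
| 0 | 1.00 | 5.0% | 4.8% | 4.5% |
| 0.005 | 1.23 | 9.4% | 9.6% | 5.2% |
| 0.01 | 1.45 | 14.5% | 14.5% | 4.8% |
| 0.02 | 1.90 | 24.9% | 25.6% | 4.8% |
| 0.05 | 3.26 | 49.2% | 49.9% | 4.6% |
| 0.10 | 5.51 | 70.0% | 70.4% | 4.5% |

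The standard error of a contrast between two surveys is understated by a factor of √k: 1.20 at v = 0.01, 1.38 at 0.02 and 1.80 at 0.05.

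**Step 5: does linear time avoid the problem?** Only in part. The site variance becomes estimable, but fixed site slopes still leave slope variation out of the error term. Under the same assumptions the simulated rates were about 10%, 14% and 27% at 0.01, 0.02 and 0.05.

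**The case against.** The strongest reply is that the written test is correct for the question it answers. Each site has its own mean at each survey, so the test conditions on site and is valid for average change in these nine facilities. The Discussion also cautions that the facilities come from two states, were not randomly selected and may not represent others. On this view the word random is merely redundant. The validity for the nine sites stands. The redundancy does not excuse the sentence, because a reader who sees site declared random will take the p-value to allow for sampling of facilities, and it does not.

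Four stronger readings are tempting, and the article does not support them:

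- **That staff are analysed as if they were independent of site.** They are not. The fixed cells remove site differences, and Step 3 shows no inflation from a shared site level.
- **That the intraclass correlation of 0.10 tells us how large v is.** The Power section does not define it as a site-by-time variance. A correlation within site would be absorbed by the cells, and a correlation within person would not concern sites at all.
- **That the error carries through all implementation conclusions.** Change in implementation measures has its own sentence and model, with no site interaction named.
- **That the H3 conclusion is itself invalidated.** H3 concerns moderation of an effect on opioid initiation, and an overall time effect does not decide it. Whether the stated model addresses H3 at all is a separate question.

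It is also fair to say that a random staff effect and the choice of degrees of freedom are details a condensed article may leave to the full analysis plan. The placement of time × site is not such a detail, because the article states it.

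**Conclusion.** The specification contradicts itself. With categorical time, the declared random site effect cannot be estimated and has no effect on the analysis. The time test then supports a statement about the average change in these nine sites and nothing wider.

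The size of the error beyond the nine sites is conditional. It is nil if all sites change alike, and about 14%, 26% and 50% at site-by-time variances of 0.01, 0.02 and 0.05. These figures rest on the assumed variances and on full response at all four surveys. Staff turnover and new recruits before each survey will alter the degrees of freedom, but not the principle. The design makes some variation in change likely, yet nothing in the article shows how much.

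This is a moderate point to correct before analysis. It does not touch the youth time-to-initiation comparisons in H1 and H2.

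**What to change.** Since site is declared random, carry that through. Fixed: time. Random: site, site × time, and staff member within site. Use small-sample degrees of freedom such as Kenward-Roger (about 24 for the overall time test), and report the site-specific trajectories as predictions from the random part.

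If only these nine facilities are of interest, declare site and time × site fixed, drop the word random, and state that the conclusion is limited to them.

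Either change takes one sentence. The first brings wider intervals and gives up the fixed-effect test of whether the nine sites changed differently from one another. The second keeps that test but gives up any inference to other facilities. The sentence should also state whether time is categorical or linear.

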To address H4 regarding economic components, an activity-based micro-costing approach is used to identify, measure, and value resources invested by participating sites, and link costs to primary and secondary study outcomes [85]. Cost comparisons represent the incremental costs of adopting SRP + TBRI relative to SRP alone. Incremental cost represents the difference in facility/provider cost after adopting the intervention vs before adopting [86, 87], and incremental effectiveness is the difference in time to opioid use initiation in TBRI relative to SRP (and between TBRI support conditions). For each facility, differences in costs and incremental cost-effectiveness ratios are estimated using multi-level general linear models (e.g., generalized linear mixed models) to account for clustering at the facility/provider and patient levels. Nonparametric bootstrapping is used to compute confidence intervals [88].

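### The H4 cost-effectiveness ratio rests on a censored time, yet the only model named is linear and no horizon or censoring rule is given

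*Protocol article*

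**What the plan says.** The economic paragraph of the Data analysis plan defines the effect side of the ratio: "incremental effectiveness is the difference in time to opioid use initiation in TBRI relative to SRP", and likewise between support conditions. It then covers estimation, facility by facility: "differences in costs and incremental cost-effectiveness ratios are estimated using multi-level general linear models (e.g., generalized linear mixed models". The reason it gives for the multilevel structure is clustering. For uncertainty, "Nonparametric bootstrapping is used to compute confidence intervals". The paragraph names no horizon, no restricted mean and no treatment of censoring.

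The preceding part of the same section analyses the same outcome for H1 and H2 by comparing survival curves. It also describes a log-rank assessment of dropout and multiple imputation, both for H1 to H3. H4 is outside that statement, although Research aims lists it with the primary hypotheses.

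Two other places bear on the point. The Power section assumes an effect "if overall opioid initiation rates are 35% (SRP) vs. 25% (all TBRI groups) at any assessed time point", with "360 youth/safe adult dyads (120 SRP, 240 TBRI), with 80 randomized to each TBRI condition". Research aims, in Aim 3, describes cost-effectiveness in terms of lower initiation rates rather than longer time to initiation.

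**The concern.** Time to initiation is known only for youth who initiate while observed. For the rest, the data show only that the time exceeds the last observation. A general or generalized linear mixed model takes a completed value as its response and has no place for that information. Whatever number is entered for these youth becomes part of the denominator of the incremental cost-effectiveness ratio.

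If the last observed day is entered, a youth who leaves the study early looks like one who started opioids early. Dropout that differs between the groups then appears as benefit or harm. The SRP and TBRI cohorts are enrolled in successive stages, so equal dropout cannot be presumed. The H1 and H2 conclusions are not affected. What is at stake is the H4 ratio and anything decided from it.

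**Working it through.** **Inputs.** From the Power section: initiation 35% (SRP) and 25% (TBRI); 120 and 240 dyads. From Overall study design and the effectiveness-trial section: follow-up to 18 months after baseline, recruitment 2 to 3 months before discharge. Assumed, because the article gives neither: exponential initiation and dropout times, and the dropout rates.

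**1. The plan's own figure built on these rates.** The plan gives no power for the ratio. It states 93% power for H1. Reading the rates as cumulative:
- Events = 120 × 0.35 + 240 × 0.25 = 102.
- Hazard ratio = ln 0.65 / ln 0.75 = 1.497.
- Schoenfeld power, two-sided 0.05 = Φ(√(102 × 1/3 × 2/3) × ln 1.497 − 1.96) = 48.5%.

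So 93% is not reproduced; about 326 events would be needed. That is a separate problem. It matters here because it leaves open how many initiations the plan expects, so step 5 repeats the check with more events.

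**2. Censored share, cumulative reading.** SRP 120 × 0.65 = 78; TBRI 240 × 0.75 = 180; together 258/360 = 71.7%.

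**3. Target with complete follow-up.** Let S be the proportion free of initiation at horizon T = 18 × 30.4375 = 547.9 days. The restricted mean is T(1 − S)/(−ln S).
- SRP: 547.9 × 0.35/0.4308 = 445.1 days.
- TBRI: 547.9 × 0.25/0.2877 = 476.1 days.
- Difference: +31.0 days.

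With no dropout, a linear model on time truncated at T estimates exactly this difference.

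**4. Observed time as response, with dropout.** If a proportion d drops out by T, mean observed time is T[1 − S(1 − d)] / [−ln S − ln(1 − d)].

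| Dropout SRP/TBRI | SRP (days) | TBRI (days) | Difference (days) |
|---|---|---|---|
| 0/0 | 445.1 | 476.1 | +31.0 |
| 20%/20% | 402.2 | 429.0 | +26.9 |
| 10%/30% | 424.1 | 403.9 | −20.2 |
| 30%/10% | 379.2 | 453.0 | +73.8 |

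Simulation of the same cases gave +31.1, +26.7, −20.1 and +73.8.

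**5. Sensitivity.**
- *Shorter horizon.* Counting about 15 months after discharge (456.6 days), the same formulas give +25.8 with no dropout, then +22.4, −16.8 and +61.5. The pattern does not change.
- *Rates read per interval and compounding.* Over four intervals, S = 0.65⁴ = 0.179 and 0.75⁴ = 0.316, and 27% of youth are censored. The 18-month differences are +64.3 with no dropout, then +56.5, +31.5 and +81.5. Over six intervals 14% are censored, and the differences are +64.9, then +57.7, +40.4 and +74.8. The bias is smaller and the sign no longer flips, but it remains.

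**The case against.** The strongest reply is that the article never says time to initiation is the response of a linear model. Grammatically, the models attach to cost differences and to the ratios, and their stated purpose is clustering. Taking the effect from the H1/H2 survival analysis would be compatible with the text. This stands as a caution: linear modelling of time is an inference, though a natural one, because the ratio contains the time difference and no other estimator is named for H4.

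A second reply is that horizon and censoring detail belongs in a fuller plan. That would dispose of simple silence. Here the article itself fixes an effect measure and a model family that do not fit together, and it states imputation for H1 to H3 only.

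Two stronger readings are tempting, and the documents support neither.
- A reader might infer that the denominator is undefined or inevitably biased. It is not. Follow-up has a fixed end, and with complete follow-up a linear model on truncated time is unbiased for the restricted mean.
- A reader might infer a roughly 100-fold range in the ratio. Under the same exponential assumption, the difference is 6.5 days among initiators only and 633 days as an extrapolated mean. But the plan commits all analyses to intent to treat with every participant included, which excludes the initiators-only version, and it nowhere proposes extrapolation.

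It is also fair that the dropout rates are not the plan's, and that 65% and 75% censoring depends on reading the rates as cumulative. The word overall in the Power section favours that reading; the stated power does not.

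**Conclusion.** The point holds in limited form. H4 names a time-to-event effect measure beside a model family that does not handle censoring, with no horizon and outside the stated imputation. The consequence is bias when youth drop out and an effect measure that is not pinned down.

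On the cumulative reading about 72% of youth are censored, and a 31-day gain could be reported as anything from about −20 to +74 days under the dropout patterns tried. Equal 20% dropout costs only about 4 days; unequal dropout does the damage. These sizes rest on exponential times, assumed dropout, an 18-month clock, and dropout time being entered as if it were the end of opioid-free time.

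Separately, the time measure in the Data analysis plan and the initiation-rate framing in Aim 3 are different effect measures and need reconciling. The change should be made, but it does not touch the primary effectiveness comparisons.

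**What to change.** Define incremental effectiveness as the difference in restricted mean opioid-free time, in days from discharge to a stated horizon within follow-up. Follow-up ends 18 months after baseline and youth enrol before discharge, so the horizon must be shorter than 18 months.

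Estimate the difference with censoring handled: either from the H1/H2 survival curves, or by pseudo-observations or inverse-probability-of-censoring weights inside the planned multilevel model. Accumulate costs over the same horizon, and resample cost and effect together in the bootstrap. State whether Aim 3's initiation rate is a second effect measure or is replaced by this one.

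The cost is a revised paragraph and a little programming, with no new data or participants. The drawback is that the effect applies only up to the chosen horizon.

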### Hybrid design: effectiveness trial

The effectiveness trial includes a comparison of youth enrolled in SRP to youth enrolled in SRP plus TBRI, whereby each facility serves as its own control. Because caregivers may need support after their youths’ release, three versions of TBRI are compared, with youth in the SRP + TBRI cohort being randomly assigned to one of three support formats: (1) TBRI Training only (no in-home TBRI support), (2) TBRI Training + Structured Coaching (4 sessions), and (3) TBRI Training + Responsive Coaching (2+ sessions, triggered by youth need/risk).

The effectiveness trial proceeds in 3 stages: Standard Reentry Practice (SRP) only (baseline control), SRP + TBRI, and Facility Sustainment (see Fig. 2). **Stage 1 - SRP**: sites engage in standard practice; study activities include youth and caregiver assessments over 18 months. Each site serves as its own control. A total of 120 youth/adult dyads are recruited across the nine sites. The length of SRP varies between 8 months (Wave 1) and 12 months (Wave 3). **Stage 2 - SRP + TBRI Intervention:** sites continue to engage in standard practice; TBRI intervention is delivered to youth and caregivers enrolled in the study; youth and caregiver assessments are conducted over an 18-month period. A total of 240 youth/adult dyads are recruited across the nine sites. **Stage 3 - Facility Sustainment**: youth/caregiver recruitment, baseline assessment, and interventions cease; youth and caregiver follow-up interviews continue; responsibility for implementing primary and secondary TBRI intervention components is transferred to the JJ facility.

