#### Randomization

Dyads are randomly assigned to TBRI support condition by the research project director using urn randomization until the recruitment target is met (minimum of 80 per arm; an average of nine per arm, per site). Urn randomization is used to balance the characteristics of youth by group on sex (male vs. female), race (Caucasian vs. other race), and primary speaking language (English vs. Spanish).

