### Study samples and recruitment

A total of nine residential facilities designed to address the behavioral and emotional needs of justice-involved youth serve as research sites for this project. Three are located in a Midwestern state and 6 in a Southwestern state in the U.S.A. Three are operated by the state JJ system, 4 by local JJ departments, and 2 by an independent agency. All sites are secure residential programs with medium security protocols, all receive referrals from JJ departments across a wide geographic region, and all provide educational, medical, and behavioral health services. At project start, 3 sites had incorporated TBRI into their trauma-informed care approach for 1–3 years, 2 were familiar with TBRI but not using principles and strategies, and 4 were unfamiliar with TBRI.

The project involves two target samples drawn from the nine facilities at rates proportional to current census/staffing levels. The effectiveness trial sample includes a total of 360 youth/caregiver (e.g., parent/guardian, extended family member) dyads recruited from participating JJ facilities over a 3-year period (approximately 10–15 dyads/year per site). Inclusion criteria include youth ages 15–18 at study enrollment who (a) are disposed to community supervision (i.e., probation) and receiving care in a secure JJ facility, (b) have no indication of active suicide risk, and (c) have worked with JJ staff to identify one caregiver that is willing to participate in the study. The implementation overlay sample includes approximately 203 (out of 810 potential participants with a 25% completion rate) JJ staff (facility staff and probation officers; an average of 22–23 per site) who work directly with youth during residential and/or community re-entry. Out of this sample, approximately 90 JJ staff (an average of 10 per site) are recruited for focus groups.

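### Cost-effectiveness ratios with bootstrap intervals are planned for each facility, but the time-to-initiation denominator is too imprecise for a reliable interval on the ratio, by site or pooled

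*Protocol article*

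**What the plan says.** The economic paragraph of the Data analysis plan defines incremental cost as the change in facility or provider cost after adopting the intervention. Incremental effectiveness is the difference in time to opioid initiation, for TBRI against SRP and also between the TBRI support conditions. The output follows: "For each facility, differences in costs and incremental cost-effectiveness ratios are estimated using multi-level general linear models". The same sentence adds that these models account for clustering by facility or provider and by patient. The next sentence gives the interval method: "Nonparametric bootstrapping is used to compute confidence intervals".

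The numbers behind the denominator are given elsewhere. Hybrid design: effectiveness trial says of Stage 1 that "A total of 120 youth/adult dyads are recruited across the nine sites" and of Stage 2 that "A total of 240 youth/adult dyads are recruited across the nine sites". Randomization gives "minimum of 80 per arm; an average of nine per arm, per site". Study samples and recruitment says that the samples are "drawn from the nine facilities at rates proportional to current census/staffing levels", so site sizes will be unequal. The Power section justifies H4 by the number of staff surveyed, not by the youth who supply the denominator.

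**The concern.** A ratio behaves well only when its denominator is clearly away from zero. As the effect difference shrinks towards zero the ratio grows without limit, and as it crosses zero the ratio jumps to the opposite extreme. Bootstrap replicates on either side of zero then have no meaningful order, and an interval read from them does not describe the uncertainty.

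The sign of the ratio is not enough either. A negative value can come from a better effect at lower cost or from a worse effect at higher cost.

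At stake is how the H4 result reads. The article expects its cost findings to inform routine delivery, and sites decide before the end of Stage 2 whether to continue the intervention. The plan fixes the ratio and the bootstrap but does not say what happens when the denominator is near or below zero.

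**Working it through.** **Inputs from the article.** 120 SRP and 240 TBRI dyads, nine sites, 80 per TBRI arm, and initiation of 35% against 25% (Power). The article gives no precision figure for the ratios, so there is none to reproduce.

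**Assumptions.** Exponential times to initiation, full follow-up, and effect measured as restricted mean time to initiation. The horizon is 15 months (discharge to Month 18) or 18 months.

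**1. Site sizes.** 120/9 = 13.3 and 240/9 = 26.7. For the arms, 80/9 = 8.9, which reproduces "an average of nine per arm, per site". Expected initiators per average site: 13.3 × 0.35 = 4.7 and 26.7 × 0.25 = 6.7.

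**2. Size of the denominator.** With cumulative risk p by horizon τ, the rate is λ = −ln(1−p)/τ and the restricted mean is p/λ.
- SRP, τ = 15: 0.35 × 15/0.4308 = 12.19 months, SD 4.60.
- TBRI, τ = 15: 0.25 × 15/0.2877 = 13.04 months, SD 4.03.
- Difference: 0.85 months.

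At τ = 18 the mean difference and the SDs all scale by 18/15 (difference 1.02), so the probabilities below do not depend on the horizon.

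**3. One site analysed alone (13 against 27).**
- SE = √(4.60²/13 + 4.03²/27) = 1.49, so z = 0.85/1.49 = 0.57.
- P(wrong sign) = Φ(−0.57) = 0.285; simulation gives 29%.
- P(95% interval covers zero) = Φ(1.96 − 0.57) − Φ(−1.96 − 0.57) = 0.91; bootstrapping the simulated data gives 88–89%.

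Variations on the wrong-sign rate:
- Risk difference in place of time: SE = √(0.35 × 0.65/13.3 + 0.25 × 0.75/26.7) = 0.155, and Φ(−0.10/0.155) = 0.26.
- True effects varying between sites with an SD equal to the mean effect: 31%.
- Smaller site, 8 against 16: 34%. Larger site, 20 against 40: 24%.
- Two coaching arms of 9, under an assumed 25% against 20%: about 42%.

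**4. Partial pooling over nine sites.** Each site estimate is shrunk towards the overall mean with weight w = σ_b²/(σ_b² + SE²), where σ_b is the between-site SD of the true effect.

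| σ_b as a multiple of the mean effect | w | Site denominator at or below zero |
|---|---|---|
| 0 | 0 | 4% |
| 0.5 | 0.07 | 5% |
| 1.0 | 0.24 | 11% |

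**5. All sites pooled (120 against 240).**
- SE = √(4.60²/120 + 4.03²/240) = 0.494, so z = 0.848/0.494 = 1.72.
- P(wrong sign) = Φ(−1.72) = 0.04.
- P(interval covers zero) = Φ(1.96 − 1.72) = 0.60; bootstrapping 300 simulated trials gives 58%.

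**6. Consistency with the stated H1 power.** The Power section's 93% would suggest a pooled denominator well clear of zero. It does not follow from the stated rates. Expected initiators are 120 × 0.35 + 240 × 0.25 = 102, and the hazard ratio is ln(0.65)/ln(0.75) = 1.50. Schoenfeld's formula then gives Φ(√(102 × 2/9) × ln 1.497 − 1.96) = 48% two-sided. About 95% appears only if all 360 youth are counted as events. That is a separate matter, but it means the 93% cannot be used to argue that the denominator is secure.

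**The case against.** The strongest reply is that the article does not plan nine separate analyses. The sentence specifies multi-level models, and clustering by facility cannot be modelled within a single facility. The Discussion also speaks of multilevel modelling across the nine sites. A reader might infer that the site ratios will often have the wrong sign. That holds only without pooling, and the text does not fix that reading; step 4 shows how far borrowing strength reduces the rate. This part of the objection stands.

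Other parts also stand:
- A reader might infer that H4 rests on nine ratios, or that facilities will be told from them whether TBRI is worth its cost. The article says neither. H4 is worded as an overall contrast.
- The article names no interval type and does not say which quantity is bootstrapped. Taking it to be the ratio is the natural reading, because the sentence follows directly on the ratios, but it is a reading.
- H4 expects TBRI to cost more. With a positive cost difference, a negative ratio has only one meaning, worse and dearer. The sign ambiguity then matters less, but the break at zero remains.
- Net benefit and acceptability curves may appear in an analysis plan that is not shown, and their absence from an article is no fault in itself.

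The objection does not rescue the interval. Strong pooling makes each site's ratio depend mainly on the common effect, and step 5 shows that this effect too is imprecise.

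**Conclusion.** The point holds as one about the stated output and its interval. It does not show that the economic data are uninterpretable: cost differences and effect differences can still be estimated and reported. Nor are small sites the whole cause, since the pooled denominator has the same weakness to a lesser degree. Moving from site to pooled estimates is therefore necessary but not sufficient, and the ratio interval itself has to be replaced.

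The sizes rest on the article's planning rates, exponential times and full follow-up. The partial-pooling range also rests on an assumed between-site SD from zero to the size of the mean effect. The 13 and 27 are averages, so sites with a smaller census would do worse, and dropout would worsen every figure. A true effect larger than planned would improve them.

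This is a worthwhile and inexpensive improvement to a non-primary analysis.

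**What to change.** In the economic paragraph of the Data analysis plan:

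1. Name the estimate pooled over the nine facilities, with facility as a random effect, as the H4 result.
2. Express its uncertainty as incremental net benefit (value per opioid-free month × months gained − incremental cost) over a stated range of values per opioid-free month, with an acceptability curve. This replaces the confidence interval on the ratio. Net benefit is linear in cost and effect, so it has no break when the effect difference is near zero.
3. Report facility-level costs, and shrunken facility-level effects or net benefit, as descriptive only.

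This costs analysis-plan wording and minor programming, with no new data. The drawback is that no facility receives a stand-alone ratio, and readers must be shown a range of willingness-to-pay values in place of a single number.
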